### Sample Size

Well-being is the primary outcome used for the power calculation. We expect to detect a significant effect on well-being between the experimental groups TL-E and TL-I compared to the WL group. Based on recent meta-analyses [17,18] and a previous comparable study [38], we expect to find a standardized effect size on well-being of 0.40 or larger. The targeted sample size is 99 participants per group (297 in total) to provide a statistical power of (1 - *β*) = 80% and a 5% significance level (two-tailed). To allow a study dropout rate of 25%, we need 132 participants in each condition and 396 participants in total for the trial.

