### Statistical Analyses

The Consolidated Standards of Reporting Trials (CONSORT) statement [91] will be used to report the results. Independent *t* tests and Chi-square statistics (X^2^) will be used to examine baseline differences between the study groups. Non-significant socio-demographic differences at baseline will indicate successful randomization. Internal consistency of the constructs will be determined using Cronbach’s alpha. To examine the efficacy of the intervention, intention-to-treat analyses will be conducted by including all participants in the analyses who have been randomized. The Expectation Maximization (EM) method will be used to impute all missing data on the continuous measures of T1, T2 and T3. This method imputes the data by maximum likelihood estimation using the observed data in an iterative process [92]. The intention-to-treat analysis will be compared with a completers-only analysis.

To examine significant differences between the 3 groups, we will perform repeated measures ANOVA in a 3 (group) x 3 (time) design with well-being (MHC-SF and FS) as the primary dependent variable and positive/negative emotions (mDES), the use of strengths (SUS), optimism (LOT-R), self-compassion (SCS-SF), resilience (BRS), and positive relations with others (SPR) as the secondary dependent variables. Significant time x group interactions will be tested with Tukey’ post hoc tests. Within-group effects (Cohen’s *d*) will be calculated by subtracting the mean post-test or follow-up score from the mean baseline score and dividing the difference by the pooled standard deviation. Between-group effects (Cohen’s *d*) will be calculated by subtracting the mean post-test or follow-up score of the experimental group from the mean post-test or follow-up score of the control group, and dividing the difference by the pooled standard deviation [93]. These effect sizes are used to gain insight into the relevance of the significant effects. To examine changes in the amount of flourishers, languishers, and moderately mentally healthy (MHC-SF), descriptive statistics will be used. Changes in categories will be tested with X^2^-statistics.

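### The between-group Cohen's d is defined from raw follow-up means without the baseline score, so it is unbiased but less precise than the data allow and does not match the time x group test it is meant to interpret (minor)

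*Protocol article*

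**What the plan says.** All of the following is in the Methods of the protocol article.

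- **Test (Statistical Analyses).** Efficacy is examined with a 3 (group) by 3 (time) repeated measures ANOVA. The follow-up step reads "Significant time x group interactions will be tested with Tukey", that is, Tukey post hoc tests. The text does not say which means those tests compare.
- **Between-group effect size (same paragraph).** Cohen's d is obtained by "subtracting the mean post-test or follow-up score of the experimental group from the mean post-test or follow-up score of the control group", divided by the pooled standard deviation. Baseline does not enter.
- **Within-group effect size (same paragraph).** This one does use baseline, but within a single arm.
- **Role of the effect sizes (same paragraph).** They serve to show how relevant the significant effects are.
- **Sample Size.** The assumption is stated as "we expect to find a standardized effect size on well-being of 0.40 or larger". From it the authors derive 99 per arm, 297 overall, and then raise this for dropout: "we need 132 participants in each condition and 396 participants in total for the trial".
- **Randomization.** Allocation is 1:1:1, stratified by gender and educational level. Baseline well-being is not a factor.
- **Table 2.** The MHC-SF, the FS and the component scales are all measured at T0, so the covariate needed for adjustment is already collected.

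**The concern.** A time x group interaction asks whether the arms differ in their course over time. The between-group d asks how far apart the arms are at one follow-up visit, wherever they started. The plan thus tests one contrast and judges its relevance by the size of another.

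Stratifying on gender and education leaves baseline well-being to chance. If one arm starts higher, part of that head start is still in the follow-up mean and enters the raw d. The T0 score would remove it and would also explain part of the follow-up variance, but the formula does not use it. These d values are the only between-group effect sizes the article defines. What is at stake is how precisely they are estimated and how well they agree with the test beside them.

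**Working it through.** **1. The plan's own figure.** Inputs from Sample Size: d = 0.40, two-sided alpha 0.05, power 80%, dropout 25%.

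- n per group = 2 × (1.960 + 0.842)² / 0.40² = 98.1, rounded up to 99.
- 99 / 0.75 = 132 per group; 3 × 132 = 396.
- Exact noncentral-t power at 99 per group is 0.7997.

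The stated size reproduces and this point does not affect it.

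**2. Setup.** Work in SD units with equal SDs at baseline and follow-up. Let b be the chance baseline difference between two arms and rho the correlation between baseline and follow-up. The documents give no rho; 0.5 to 0.7 is assumed, with 0.3 and 0.8 as outer values. Differences are taken as experimental minus control, so a benefit is positive. The article's formula has the opposite sign, which changes no size below. Sampling error in the SD itself is ignored.

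**3. What each estimate carries, given b.** With true effect δ:

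- raw follow-up d: δ + rho × b
- change-based d: δ + (rho − 1) × b
- baseline-adjusted d: δ

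Averaged over randomizations b is zero, so all three estimate δ. In 20,000 simulated trials per setting with δ = 0.40, the means of all three were 0.399 to 0.400.

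**4. Size of the chance imbalance.** SD of b = √(2/n). At 132 per arm this is √(2/132) = 0.123; at 99 per arm, √(2/99) = 0.142.

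**5. Gap between the raw d and the adjusted d.** The gap is rho × b, with SD rho × √(2/n). The chance that it exceeds t in size is 2 × [1 − Φ(t / SD)].

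| n per arm | rho | SD of gap | more than 0.1 SD | more than 0.2 SD |
|---|---|---|---|---|
| 132 | 0.3 | 0.037 | 0.7% | <0.1% |
| 132 | 0.5 | 0.062 | 10% | 0.1% |
| 132 | 0.7 | 0.086 | 25% | 2% |
| 132 | 0.8 | 0.098 | 31% | 4% |
| 99 | 0.5 | 0.071 | 16% | 0.5% |
| 99 | 0.7 | 0.099 | 31% | 4% |

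For example, at 132 per arm and rho 0.7: 0.1 / 0.0862 = 1.16, two-sided tail 0.25. The simulation gave 0.101 (rho 0.5) and 0.245 (rho 0.7) for a gap above 0.1 SD at 132 per arm.

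**6. Precision.** SE(raw) = √(2/n); SE(adjusted) = √(2/n) × √(1 − rho²). At 132 per arm:

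- raw: 0.123
- adjusted, rho 0.5: 0.123 × 0.866 = 0.107, interval 13% narrower
- adjusted, rho 0.7: 0.123 × 0.714 = 0.088, interval 29% narrower
- outer values: 0.117 at rho 0.3 (5% narrower) and 0.074 at rho 0.8 (40% narrower)

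**7. One illustration.** True effect 0.40, experimental arm starting 0.20 SD higher. The raw d is 0.40 + 0.5 × 0.20 = 0.50 at rho 0.5, or 0.54 at rho 0.7. The adjusted d is centred on 0.40 in both cases.

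**The case against.** The strongest reply is that a raw follow-up d is a valid, clearly defined and unbiased measure in a randomized trial, so choosing another is preference. Unbiasedness stands and sets the limit of this point. A reader might infer that the plan's d is biased, or that it measures a different effect from the one tested. Neither follows: over randomizations the raw and change-based contrasts estimate the same population effect.

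A reader might also infer that the interaction test removes baseline imbalance and that only d retains it. It does not. The change contrast carries (rho − 1) × b, in the opposite direction, and at rho 0.5 it is as far off as the raw d. Nor should the problem be sized by the gap between raw d and a change score. That gap is b itself and exceeds 0.1 SD in about 42% of comparisons at 132 per arm, but this overstates what adjustment would alter. The relevant gap is rho × b.

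A third tempting reading is that an arm that merely started higher could yield a significant result with an inflated d. Such an arm tends to show less change, so the interaction works against it, and d is used to interpret significant effects.

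Two further replies carry some weight. The sample size rests on a plain two-group comparison without baseline, so the raw d matches that basis. And if the Tukey tests compare means at each visit, the raw d matches that step too, though still not the interaction that triggers it. The article also plans baseline tests and within-group d values, but neither gives a baseline-adjusted comparison of arms.

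**Conclusion.** The point holds as a minor one. The article fixes a between-group effect size that leaves out a covariate it already collects, and uses it to interpret a test that does use baseline. The consequences are lost precision and a chance departure from the adjusted estimate, at the sizes in steps 5 and 6 of the working. They are not a bias in the plan.

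The sizes rest on an assumed rho of 0.5 to 0.7, equal SDs and 132 per arm. With a rho near 0.3 the matter is close to negligible; with 0.8, or with only 99 per arm contributing, it is somewhat larger. The conclusion does not depend on which means the Tukey tests compare.

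**What to change.** For each arm contrast at T1 and T2, compute the between-group d from a baseline-adjusted mean difference: an ANCOVA with the T0 score as covariate, or an equivalent mixed model. Divide by an unadjusted pooled SD named in advance (for example the pooled T0 SD) and give a 95% CI. The repeated measures ANOVA, with T0 as one of its time levels, does not itself yield this estimate, so the adjusted model has to be run alongside it or in its place, and the text should say which. Keep raw means, SDs and the raw d in a descriptive table for readers and meta-analysts.

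The cost is one additional simple model per outcome and time point and a revised sentence in Statistical Analyses. No new data are needed and the sample size does not change.

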#### Secondary Outcomes

The MHC-SF is also used to measure the amount of flourishing [13,43]. Flourishers score 4 or 5 on 1 or more items on the emotional well-being subscale in combination with a score of 4 or 5 on 6 of the 11 remaining items. Languishers are those with scores of 0 or 1 on these subscales, and individuals who are neither flourishing nor languishing are labelled as moderately mentally healthy.

Depressive and anxiety symptoms will be measured with the HADS [44]. Each subscale consists of 7 items, 14 items in total. Answer categories differ per item, but all items have 4 answer categories with scores ranging from 0-3. Item scores are summed into a total scale score for anxiety (range 0-21) and depression (range 0-21). The HADS is a widely validated instrument and can be used as a screening instrument in different populations [70,71]. A cut-off score of 10 and above on each subscale is generally used to identify individuals with at least mild depressive or anxiety symptomatology [44,70].

Positive and negative emotional states will be assessed with the modified Differential Emotions Scale (m-DES), which measures 8 groups of positive emotions and 8 groups of negative emotions on a 7-point scale (1 = not at all, 7 = very intense). Total mean scores will be computed. Although the DES is validated and widely used, the m-DES has not yet been validated [72].

The Strength Use Scale (SUS) is a 14-item scale to assess participants’ use of their strengths in a variety of settings [73]. Scores range from 1 (strongly disagree) to 7 (strongly agree) with a total summed score of 14 to 98. The SUS possesses high internal consistency and long-term stability [74].

Optimism will be assessed with the 10-item Life Orientation Test-Revised (LOT-R) [75,76]. Items are rated on a 5-point scale ranging from 0 (strongly disagree) to 4 (strongly agree) and indicate participants’ evaluation of positive expectations about the future. There are 4 filler items which are excluded from analysis. Scores on the 6 items are summed into a total optimism score ranging from 0-24. The LOT-R has shown predictive and discriminant validity [75].

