Mediator and moderator analyses will be performed as described by Hayes [94,95]. Mediator analyses will be conducted to investigate which of the specific components of the intervention—positive emotion, use of strengths, optimism, self-compassion, resilience, and positive relations—contribute to its efficacy and mediate overall well-being. Moderator analyses will be conducted to examine which specific subgroups will improve most (or least) on well-being and flourishing from participation in one of the experimental groups. The independent variables of gender, educational level, life-events, personality traits, level of adherence to the intervention, and participation satisfaction will be entered as moderators in regression analyses.

A cost-effectiveness analysis will be conducted from a societal perspective. For each condition, the mean annual health care costs (MCQ), costs due to productivity losses (PCQ), and intervention costs will be calculated on an annual per capita basis for the reference year 2014. All costs will be expressed in Euro (€). The incremental cost-effectiveness ratio (ICER) will be calculated using a bootstrap approach. Then, a cost-effectiveness acceptability curve will demonstrate the probability of the cost-effectiveness of TL-E and TL-I compared to WL, for a range of willingness-to-pay (WTP) ceilings. All tests will be two-sided and will use alphas of 0.05. All data-analyses will be performed with SPSS version 21.0 or higher.

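### The ordered languishing / moderate / flourishing categories are to be tested with X² and no ordinal test is named; under a uniform shift this costs roughly 9 to 12 power points, and adding an ordinal test is a cheap improvement.

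*Protocol article*

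**What the plan says.** The Secondary Outcomes section introduces the classification with "The MHC-SF is also used to measure the amount of flourishing". Flourishers are the top level and languishers the bottom level, and "individuals who are neither flourishing nor languishing are labelled as moderately mentally healthy". The order is therefore part of the definition.

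The Statistical Analyses section then states "To examine changes in the amount of flourishers, languishers, and moderately mentally healthy (MHC-SF), descriptive statistics will be used", followed by "Changes in categories will be tested with X^2^-statistics". It does not give the layout of the table (three levels, or flourishing yes/no) or the time point, and it mentions no trend version. On error rates the section says "All tests will be two-sided and will use alphas of 0.05".

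The Sample Size section concerns continuous well-being only: "we expect to find a standardized effect size on well-being of 0.40 or larger". No power and no expected category shares are given for the categories.

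**The concern.** A Pearson X² takes the same value if the three labels are shuffled. A move from languishing to moderate and a move from moderate to flourishing are not added up as improvement in one direction. On a table of three groups by three categories the test has 4 degrees of freedom, where a rank test has 2. For one book arm against the waiting list the figures are 2 and 1. The hypothesis in the This Study section is directional, with email support expected to be superior to the waiting list.

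The X² is the only between-group efficacy test named for the categories, and flourishing is part of the stated research aim. The trial is sized for the continuous scale, so the category comparison starts with less power. What is at stake is a higher chance of missing a real shift in categories. Validity is not in question.

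**Working it through.** **Inputs from the article.** d = 0.40, two-sided 5%, 80% power, 99 per group, 25% dropout, 132 per group, three arms 1:1:1. EM imputation is planned for continuous measures only, so I take 99 and 132 as the two ends for the number per group with category data.

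**Assumed.** Waiting-list (WL) category shares: 12 splits, languishing 2–30% and flourishing 5–30%.

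**The plan's own figure.** n = 2(1.96 + 0.8416)² / 0.40² = 15.70 / 0.16 = 98.1, so 99 per group. Power at 99 is 80.4% (normal) or 80.0% (t). 99 / 0.75 = 132. Both stated figures reproduce.

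**Set-up.** Let p_L and p_F be the WL shares languishing and flourishing. The cut-points on a standard normal scale are c1 = Φ⁻¹(p_L) and c2 = Φ⁻¹(1 − p_F). A book arm shifted by 0.40 has shares Φ(c1 − 0.40) and 1 − Φ(c2 − 0.40). Example with 5% and 20%: c1 = −1.645 and c2 = 0.842, so the book arm has Φ(−2.045) = 2.0% languishing and 1 − Φ(0.442) = 32.9% flourishing, with about 65% moderate.

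For each scenario, 20,000 simulated trials compared Pearson X² with a rank test: Wilcoxon for two arms, Kruskal-Wallis for three. The Wilcoxon stands in for the two-group proportional-odds model, whose score test it is.

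**Uniform shift, WL 5/75/20% (languishing/moderate/flourishing).**

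| Comparison | n per group | X², 3 levels | Rank test | Loss (points) |
|---|---|---|---|---|
| One book arm vs WL | 99 | 50.9% | 61.4% | 10.5 |
| One book arm vs WL | 132 | 63.8% | 73.5% | 9.7 |
| Both book arms and WL | 99 | 52.1% | 62.9% | 10.8 |
| Both book arms and WL | 132 | 66.6% | 76.5% | 9.9 |

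**Over all 12 splits.** For two arms, X² has 27–59% power against 38–69% for the rank test at 99 per group (loss 9.9–11.8 points). At 132 it is 36–73% against 48–82% (loss 8.8–12.1). With three arms and both book arms at 0.40, the loss is 9.9–12.1 at 99 and 8.6–12.4 at 132. With graded effects of 0.40 / 0.20 / 0 it is 9.3–12.0 and 10.7–12.0.

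**Cross-check by noncentral chi-square.** The noncentrality that gives 80% power on 1 df gives 70.9% on 2 df (9.1 points). The one that gives 60% on 2 df gives 48.5% on 4 df (11.5 points).

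**Effect at the moderate-to-flourishing boundary only, one book arm vs WL, n = 99.**

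| WL → book arm (%) | X², 3 levels | Rank test | X², flourishing yes/no |
|---|---|---|---|
| 5/85/10 → 5/73/22 | 54.3% | 50.1% | 64.7% |
| 5/75/20 → 5/60/35 | 56.7% | 57.1% | 66.9% |
| 10/70/20 → 10/55/35 | 57.5% | 47.9% | 65.9% |
| 20/60/20 → 20/45/35 | 60.3% | 36.4% | 66.8% |

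Here the rank test ranges from about equal to much worse. The largest shortfall is 28.9 points (three arms, 132 per group, last row). If both extremes grow, X² has 59–79% power and the rank test 8–11%.

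**Flourishing yes/no under the uniform shift.** A 1-df X² on flourishing alone had less power than the two-arm rank test in all 12 splits, by 2.5 to 26.9 points. The gap is smallest when languishing is rare.

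**The case against.** The strongest reply is that the article does not fix the test being criticised. It says X² statistics, in the plural, with no table. That could mean flourishing yes/no, where no order is ignored, or a trend version, since the linear-by-linear test is itself a chi-square statistic. This stands as a limit: the 9 to 12 points apply to an ordinary X² on three levels. It does not remove the point, because the preceding sentence names all three categories and no trend test is mentioned. Under a uniform shift, flourishing yes/no also trails the ordinal test, though by only about 2.5 to 6.5 points for 20% flourishing and 2–5% languishing at 99 per group.

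A reader might infer that X² gives up this power at no benefit. The working does not support that. X² keeps power for effects at one boundary or in both extremes, and flourishing, the category in the research aim, lies beyond one boundary. The article's only stated effect is a difference in mean well-being. That makes a uniform shift a reasonable case to examine, but it does not establish one.

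It is also fair to say that a general shift is already tested, with more information, on the continuous MHC-SF score. Replacing X² by an ordinal test alone would leave flourishing itself without a test. Both objections stand and shape the fix.

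**Conclusion.** The point holds as a conditional one. If the test is an ordinary Pearson X² on the three levels, and the effect is a uniform shift of d = 0.40, it loses roughly 9 to 12 power points against an ordinal test (8.6 to 12.4 over the splits examined with every book arm at 0.40). The figure rests on category shares that are assumed. It shrinks or reverses if the effect sits only between moderate and flourishing.

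A reader might also infer that the plan is wrong here or that its inference is invalid. It is not: in null simulations with these category tables both kinds of test rejected in 3.7–5.8% of runs, near the nominal 5%. The Methods list the category measure as secondary. The Abstract's placing of flourishing among the primary outcomes is a separate inconsistency and does not raise the weight of this point. This is a low-cost improvement to a secondary analysis.

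**What to change.** In Statistical Analyses, replace the sentence on X² with wording to this effect: the three-level MHC-SF category will be compared between groups at T1 and at T2 with a proportional-odds model with group as factor (or, for each pair of groups, a linear-by-linear X² test); the proportion flourishing will be compared between groups by a separate X² test; and the percentage in each category will be reported per group and time point. T1 and T2 are the time points before the waiting-list group receives the book.

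The cost is a sentence or two. No further data or participants are needed, and SPSS, which the plan already names, runs both analyses. The common odds ratio assumes a similar shift at both cut-points, which the tabulated percentages let readers judge. One more secondary test is reported, so the text should say which of the two addresses the flourishing aim.

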### This Study

This study will examine a comprehensive multicomponent positive psychology-based self-help book with email support. The self-help book is entitled, “This is your life” (TL) [40] and targets 6 key components in positive psychology: positive emotion, use of strengths, optimism, self-compassion, resilience, and positive relations. We will compare a condition wherein participants receive the book with weekly asynchronous and tailored email support (TL-E) to a condition wherein participants receive the book with a weekly email with information (TL-I). Both groups will be compared to a waiting list control condition (WL). Our research aim is to evaluate the efficacy of the multicomponent self-help book with or without email support in terms of well-being and flourishing in an RCT (NTR4297) and to evaluate which of the included well-being components in the self-help book contribute to its efficacy. We expect that TL-E will be equivalent or superior to TL-I and superior to WL at post-test and 6 months follow-up, and that the effects will be sustained at 12 months follow-up.

This study will add to current knowledge in 3 ways. First, it will be conducted in a sample with low or moderate levels of well-being without moderate or severe clinical symptomatology, which is a potential “happiness-seekers” group [41] that has not previously been studied in PPIs [17,18,27]. Second, this study will gain insight into the working mechanisms underlying the intervention by evaluating which of the included well-being components in the self-help book (ie, positive emotion, use of strengths, optimism, self-compassion, resilience, and positive relations) contribute to its efficacy and by examining individual differences in demographic characteristics, number of life events, personality traits, and adherence rates. Third, this study will examine if the innovative format used in this study (ie, self-help book with relatively inexpensive email support) is a cost-effective approach for enhancing well-being and flourishing compared to a waiting list control group, since little is known about the cost-effectiveness of PPIs [26].

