#### Control group

Participants in the control group will be on a waiting list for the first 6 months of the study and will receive the self-help book after they complete the 6-month follow-up assessment. For the sake of comparison at the long-term follow-up, the control group will also receive the information emails in the same way provided in the TL-I group.

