### Measures

For a brief overview of all outcome measures and assessment times, see Table 2. Because one of our aims is to examine the working mechanisms underlying the intervention, which requires assessing all included positive psychology components, measures are selected on brevity and availability in the Dutch language.

**Table 2 table2:** Intended questionnaires and assessment times.

			T0	T1	T2	T3
Questionnaire	Measurement	Screening	Pre-test	Post-test	Follow-up^a^	Follow-up^b^
MHC-SF	Well-being/ flourishing	X	X	X	X	X
FS	Social-psychological well-being		X	X	X	X
HADS	Symptoms of depression and anxiety	X			X	X
m-DES	Positive and negative emotions		X	X	X	X^d^
SUS	Use of strengths		X	X	X	X^d^
LOT-R	Optimism		X	X	X	X^d^
SCS-SF	Self-compassion		X	X	X	X^d^
BRS	Resilience		X	X	X	X^d^
SPR	Positive relations		X	X	X	X^d^
EPQ-RSS	Extraversion and neuroticism		X			
NEO-FFI	Conscientiousness		X			
MCQ	Direct medical consumption costs		X	X^c^	X^c^	X
PCQ	Non-medical productivity costs		X			X
Brugha Life-events	Positive and negative life-events		X	X	X	X
CSQ-8	Client satisfaction			X^d^		
Process evaluation	Invested time, adherence, positive changes			X^d^		X^e^
	Level of (continued) use					X
Demographics	Gender, age, education, marital status, living situation, ethnicity, daily activities	X				

^a^ 6 months after T0.

^b^ 12 months after T0.

^c^ Only medical health care costs are assessed, not medication costs.

^d^ Only assessed in the experimental groups, not the control group.

^e^ Only assessed in the control group, not the experimental groups.

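### From month 6 the annual cost-effectiveness comparison with the waiting list is one of immediate versus delayed access, which the plan does not say, and Table 2 does not collect the data for a full 6-month societal ICER

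*Protocol article*

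**What the plan says.** All references are to the protocol article.

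- **Perspective and costs (Statistical Analyses).** "A cost-effectiveness analysis will be conducted from a societal perspective". For each condition, annual health care costs (MCQ) are calculated, and "costs due to productivity losses (PCQ), and intervention costs will be calculated on an annual per capita basis for the reference year 2014". The acceptability curve is to show "the probability of the cost-effectiveness of TL-E and TL-I compared to WL".
- **Aim (This Study).** The third stated contribution is to examine whether the format "is a cost-effective approach for enhancing well-being and flourishing compared to a waiting list control group".
- **Comparator (Control group).** "Participants in the control group will be on a waiting list for the first 6 months of the study". Once they have completed T2 they are sent the book, and they also get the TL-I emails so that a long-term comparison can be made.
- **Cost instruments (Measures, Table 2).** The PCQ (productivity) is marked at T0 and T3 only. The MCQ is marked at all four assessments, but T1 and T2 carry footnote c: "Only medical health care costs are assessed, not medication costs".

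The article does not set a 6-month horizon for the comparison with WL. It does not say at which assessment the effect in the ICER is read, what recall periods the PCQ and MCQ use, or whether the book and emails given to WL in months 6 to 12 count as WL intervention costs.

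**The concern.** An ICER against a comparator is interpretable only if the comparator stays the same over the period in which costs and effects accrue. Here WL is a control without the book for the first half of the costing year and a delayed TL-I arm for the second half. An annual ICER therefore estimates the value of having the book now rather than six months later. That is a legitimate question, but a reader of the stated aim would not know that it is the one being answered.

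The usual remedy is to stop the comparison when the control arm crosses over. The measurement schedule blocks it, because two components of a societal cost total have no post-baseline measurement before crossover. An analysis plan written later could change the horizon or the label, but it could not supply data that were never collected.

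The stake is the cost-effectiveness claim, which is one of the study's three declared contributions.

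**Working it through.** **1. The plan's own figure.** The article gives no figure for the cost-effectiveness analysis. The sample size does reproduce. With d = 0.40, two-sided alpha 0.05 and power 80%, n = 2(1.960 + 0.842)² / 0.40² = 98.1, so 99 per group (power 0.804 at 99). Then 99 / 0.75 = 132 and 3 × 132 = 396. I use d = 0.40 and 99 per arm below.

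**2. Horizon against treatment status of WL.**

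| Period | TL-E | TL-I | WL |
|---|---|---|---|
| T0 to T2 (months 0-6) | book + counsellor emails | book + information emails | waiting |
| T2 to T3 (months 6-12) | follow-up | follow-up | book + information emails |

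The share of the costing year after WL is offered the book is 6/12 = 50%. This is a share of time; no cost amounts are given.

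**3. Cost data against the crossover.**

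| Component | T0 | T1 | T2 | T3 |
|---|---|---|---|---|
| Health care use (MCQ) | yes | yes | yes | yes |
| Medication (MCQ) | yes | no | no | yes |
| Productivity (5 PCQ items) | yes | no | no | yes |

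Post-baseline measurements of productivity and medication up to T2: none. The only one of each is at T3. If its recall is 6 months or less, it covers only time after crossover. If it is longer, it mixes the two periods and cannot be split.

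**4. What happens to the contrast if the effect is read at T3.** This is an illustration. Let c be the per-person cost of book plus information emails (the same in TL-I and WL), p the share of WL that takes up the book after T2, and f the share of the 0.40 effect that those participants gain by T3. Both p and f are assumed. I also assume that TL-I still holds its 0.40 at T3.

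- TL-I minus WL, intervention cost: c up to T2; c(1 − p) over 12 months if WL's package is counted.
- TL-I minus WL, effect: 0.40(1 − pf).

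| p | Cost difference | Effect, f = 0.5 | Effect, f = 1 |
|---|---|---|---|
| 0.50 | 0.50c | 0.30 | 0.20 |
| 0.75 | 0.25c | 0.25 | 0.10 |
| 1.00 | 0 | 0.20 | 0 |

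With 99 analysed per arm, the standard error of a standardised difference is √(2/99) = 0.142. An effect of 0.40 is 2.8 standard errors from zero, 0.20 is 1.4, and 0.10 is 0.7.

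**5. The unstated costing rule matters.** Take p = 0.75 and f = 0.5, so 1 − pf = 0.625. Relative to c/0.40 in the controlled period, the ICER on intervention cost alone is multiplied by 0.25/0.625 = 0.40 if WL's package is counted, and by 1/0.625 = 1.60 if it is not. The distortion can go in either direction.

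**6. TL-E.** WL never receives counsellor support, so the cost contrast with TL-E cannot fall to zero. Any effect that comes from the support also remains. The shrinkage in step 4 therefore applies most fully to TL-I.

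**The case against.** The strongest reply is that nothing is hidden. The Control group section states the delayed access openly and gives the emails for the sake of a long-term comparison. The aim and the analysis both name a waiting list. This stands: a reader might infer that the article promises an ICER against no intervention and then contradicts itself, but it never uses that term. The fault is an unlabelled change of comparator within the costing year.

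Second, an annual per capita basis may be only a costing unit, and the effect could be read at T2. The efficacy model has three time points although there are four assessments, most naturally T0 to T2. This also stands, so the loss of effect in step 4 is conditional. It does not help with productivity or medication costs, whose only post-baseline measurement is at T3.

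Third, a reader might infer that the ICER will collapse or become undefined. The documents do not support that. Uptake and catch-up are not given, full catch-up is only one scenario and fits TL-I better than TL-E, and a negative effect difference is an ordinary point on the cost-effectiveness plane. Only a difference of exactly zero leaves the ratio undefined, and an acceptability curve based on net benefit can still be computed.

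Fourth, a reader might take the expectation that "the effects will be sustained at 12 months follow-up" to be untestable without an untreated arm at T3. It can be read as maintenance within the treated groups, for which the plan provides within-group effect sizes. Only a T3 effect size against WL, if one is reported, shares the problem.

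**Conclusion.** The point holds as a should-fix with two parts.

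1. Half of the costing year compares immediate with delayed access, and the plan does not say so or state how WL's own intervention costs are counted. This follows from the text without assumptions, provided that the annual basis means the 12 months of follow-up.
2. A full 6-month societal ICER cannot be built from Table 2, because productivity and medication have no post-baseline measurement before crossover. This holds whichever meaning of annual is intended.

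How far a 12-month ICER moves cannot be fixed from the documents. On the plan's 0.40, the T3 effect contrast for TL-I ranges from 0.30 to 0 over the assumed uptake and catch-up values. The protocol itself treats WL as a treated arm at T3: Table 2 drops the component measures for WL there and adds its process evaluation. The cost analysis should do likewise.

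The cost-effectiveness analysis is not primary and does not determine the sample size. Efficacy comparisons at T1 and T2 precede the crossover and are unaffected.

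**What to change.** - Make T0 to T2 the horizon for TL-E and TL-I versus WL, with costs and effects both ending at T2.
- Add the 5 PCQ items and the MCQ medication items to the T2 questionnaire in all arms.
- If T2 has already been collected, report a 6-month analysis of health care plus intervention costs, and do not call it societal. This may well apply: data collection is to end in June 2015, so the last T2 assessments would fall about six months before that.
- Label any 12-month ICER or acceptability curve against WL as immediate versus delayed access, and count WL's book and emails in its costs. Give any T3 between-group effect size against WL the same label.

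The cost is a few extra items at T2, some rewording, and a shorter main horizon for the economic comparison.
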